### Interventions

#### Intervention arm

Adolescents in the study intervention arm receive a manualized package of care that consists of: behavioral activation and problem-solving treatment; parenting skills training; and social and parenting skills support provided by a “neighborhood mother”. The behavioral activation and problem-solving treatment is delivered in six sessions during the antenatal period, consisting of three weekly sessions followed by three fortnightly sessions for those with EPDS scores of 12–17, or all six sessions delivered weekly for those with EPDS scores > 17. Supplemental sessions may be delivered if, during the 6-week postnatal visit, the providers find that the mother still has significant levels of depression (EPDS score of 6 or more). The number and frequency of these sessions are determined by the providers based on the level of depression (see Fig. 2). Treatment adherence is promoted by providers calling or sending text messages to their patients reminding them of appointments and agreed homework tasks from the PST sessions. This approach and the format of the problem-solving treatment are similar to what we used in our earlier RCT for perinatal depression. The parenting skills training is delivered in two ways: as a component of the problem-solving treatment which is provided in face-to-face sessions; and through mobile phone calls and texts (as appropriate) delivered in the postnatal period. There is a core set of themes to guide the provider during the calls, but attention to the particular needs or deficits of individual adolescent mothers is also addressed during the calls. The core themes consist of: personal and health care needs during pregnancy, including nutrition, rest, exercise, avoiding alcohol, and self-medication; preparing for childbirth; early signs of common ill health during pregnancy and in the infant; care of the newborn; infant feeding (including good and common bad practices to avoid); immunization schedule; stimulating and responding to infant’s needs; and dispelling cultural myths and taboos that are either harmful or unhelpful to good parenting. Many of the materials to inform the contents of the parenting skills training have been designed to address deficits in parenting skills among adolescent mothers as observed in our previous RCT. The materials also reflect information obtained during the formative qualitative activities. Providers make fortnightly calls starting shortly after the 6-week postnatal clinic visit of the mother and child, and continue until at least the 6-month postnatal outcome assessment. (We will encourage providers to continue with this, as needed, even after the discontinuation of the mother from the trial at the end of the 6-month postnatal period.)

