### Outcome evaluation and instruments

Outcome assessments are conducted in participants’ homes or at any other place of their preference. Outcome assessors have no involvement in the delivery of the intervention and conduct the assessment blind to the participant’s study arm. Assessments of participants are being conducted at baseline (within 72 h following enrollment) and at the 3-month and 6-month postnatal periods (Table 1). Details of childbirth are obtained from the facility where delivery takes place, from the mother, and by direct measurement of the baby soon after childbirth following notification of our team by the maternal care providers.

The primary outcomes, determined at 6 months postnatal, are 1) the difference in the level of depressive symptoms as assessed with the EPDS [22] between participants in the intervention and care as usual groups; and 2): level of parenting skills as measured by the total and subscale scores on the HOME-IT.

Assessments of secondary outcomes, to be conducted at 3 or 6 months (see Table 1), consist of the following: depression remission rates (EPDS score < 6); level of disability as assessed using the WHO Disability Assessment Scale [23]; maternal attitude and adjustment to pregnancy and motherhood as measured with the Maternal Adjustment and Maternal Attitude scale (MAMAS) [24]; quality of life using the short form of the WHO Quality of Life scale, WHOQoL-BREF; and the extent of mother–infant interactions assessed using the Postnatal Bonding Questionnaire (PBQ) [18]. The family planning and new pregnancy questionnaire (designed by the investigators) will assess what measures, if any, the adolescents have taken to prevent getting pregnant soon after the index childbirth. The Perinatal Infant Care Social Support scale (PICSS) [19] will rate the availability of social support for the adolescents as they navigate the challenge of motherhood. Assessments of the infants will include weight, height, and head circumference at birth and at 3 and 6 months of age, nutrition (history of breastfeeding), vaccinations received, and the child’s social, cognitive, and physical developmental milestones.

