### Blinding and protection against sources of bias

The following steps are being undertaken to reduce the risk of bias in this trial. First, allocation was performed by a statistician with no other involvement in the study. Second, it is recognized that allocation concealment and selection bias can be a problem in cluster randomized trials when not all participants are consented and recruited prior to the allocation of clusters. Consecutive attendees at the randomized primary maternal care clinic (MCC) are being invited to participate. Study invitees are not informed of their allocation until after establishing eligibility and providing consent to participate. Consent rates in terms of both proportion and disease severity of eligible patients in both arms of the trial are being monitored. Third, the study is designed to ensure that the risk of contamination between arms is low as patients are unlikely to move from a control to an intervention clinic due to their geographical spread and because there has been no publicity regarding the availability of the intervention in other clinics. Fourth, even though blinding of participants is clearly not possible given the nature of the intervention, however, outcome assessors are not involved in delivering the intervention and are rotated between trial participants to collect data. Fifth, our primary outcomes are the severity of depression symptoms and level of parenting skills at 6 months postnatal. We are collecting the outcome data from every participant not known to have died at the time of follow-up and who has not withdrawn consent or otherwise become unavailable, regardless of compliance with allocated treatment. Sixth, we anticipate some non-collection of primary outcome data, and while the primary intention-to-treat analyses will be without imputation of missing data, sensitivity analyses will investigate various assumptions about the missing data.

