### Sample size determination for the RCT

The primary outcome considered in calculating the sample size is the level of depressive symptoms as assessed with the EPDS total score at 6 months postpartum. Based on the results of our recently concluded cluster randomized controlled trial of interventions for perinatal depression in primary care in Nigeria (EXPONATE) [15] showing a standard deviation (SD) for the EPDS score of 4.5, we estimate that a mean difference of 2.0 in the EPDS score between the two arms at 6-month postnatal follow-up will represent a clinically significant difference in depression symptoms, giving a target effect size of 0.44. About 6 months into recruitment to the current trial, there was an imbalance in the ratio of participants recruited to the trial of about 1.5 in favor of the intervention arm. An uninflated sample size of 102 in the intervention arm and 68 in the control arm will be required to provide a power of 80% at an α level of 0.05. Based on prior experience, we expect to recruit seven adolescent participants per cluster over 18 months. To take account of the cluster design, we inflate the estimated cluster size by 1 + [(*k* – 1) × ICC)], where *k* is the cluster size for analysis and ICC is the intracluster correlation coefficient. In previous use of the EPDS, we obtained an estimate of 0.03 for the ICC. Using the resulting design effect of 1.18, the estimated inflated sample size is 200 (170 × 1.18). Taking account of a projected attrition not exceeding 15% at 6 months postnatal and a resulting sample size of 230, we plan to recruit from 30 clusters.

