#### Quantitative analysis

The analysis and presentation of the trial will be in accordance with CONSORT guidelines [32], with the primary comparative analyses being conducted on an intention-to-treat basis and due emphasis placed on confidence intervals for the between-arm comparisons. A full analysis plan will be developed prior to completion of data collection and discussed and agreed with the TSC.

We will use descriptive statistics to assess the balance between the trial arms at baseline for both MCC and individual participant characteristics. In order to take appropriate account of the hierarchical nature of the data, we will use multivariate mixed-effects regression models (logistic or linear dependent on outcome type) to estimate recovery from depression at 6 months for the intervention group versus the control arm, adjusting for baseline depression and randomization variables. In a secondary analysis, we will further adjust for any variables that were imbalanced between trial arms at baseline. We will analyze continuous outcomes (EPDS and GAD-7) over the 6-month postnatal follow-up period using repeated-measures analysis by including follow-up occasion as a random effect in the regression model. The primary outcome will first be analyzed by intention to treat without imputation. However, we will conduct sensitivity analyses to assess the potential effect of missing data using multiple imputation methods. No interim analysis is planned except when required to explore any undesired effect that may arise during the course of the trial and such analysis is deemed necessary and approved by the TSC.

We will use descriptive statistics to explore provider competence, as assessed by ENACT. We will evaluate the provider determinants of competence by determining the demographic predictors of scores on ENACT using regression analysis.

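### Read as a single-time-point model without imputation, the primary 6-month EPDS comparison leaves out women who have only a 3-month score, and the repeated-measures analysis that could use them is not named as primary

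*Protocol article*

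**What the plan says.** In the protocol article, the EPDS primary outcome (Outcome evaluation and instruments) is "the difference in the level of depressive symptoms as assessed with the EPDS [22] between participants in the intervention and care as usual groups", determined at 6 months postnatal. The same section and Table 1 place the EPDS at three occasions: "Assessments of participants are being conducted at baseline (within 72 h following enrollment) and at the 3-month and 6-month postnatal periods".

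The missing-data rule appears twice. Under Blinding and protection against sources of bias: "while the primary intention-to-treat analyses will be without imputation of missing data, sensitivity analyses will investigate various assumptions about the missing data". Under Quantitative analysis: "The primary outcome will first be analyzed by intention to treat without imputation". The sentence that follows the second statement adds multiple imputation as a sensitivity analysis.

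Quantitative analysis describes two models that could carry the EPDS result:

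- A mixed-effects regression, logistic or linear, that estimates recovery from depression "at 6 months for the intervention group versus the control arm, adjusting for baseline depression and randomization variables". It is followed by a secondary analysis with further adjustment. No 3-month EPDS term is mentioned.
- A repeated-measures analysis of EPDS and GAD-7 over the postnatal follow-up, with occasion entered as a random effect. It is labelled neither primary nor secondary, and no arm-by-occasion term is stated.

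The sample-size section sets the expected loss: "Taking account of a projected attrition not exceeding 15% at 6 months postnatal".

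**The concern.** A mixed model of the 6-month score alone, without imputation, uses only women who have that score. A woman assessed at 3 months and lost by 6 months adds nothing to it, although her 3-month EPDS is probably the best measured predictor of what is missing. The estimate is then unbiased only if, given arm, baseline EPDS and the randomization variables, being missed at 6 months is unrelated to the 6-month score.

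Contact differs by arm over the period in which 6-month data would be lost. In the intervention arm, "Providers make fortnightly calls starting shortly after the 6-week postnatal clinic visit of the mother and child", and these calls continue until at least the 6-month assessment. Usual care has no such structured contact. That makes arm-differential loss possible; it does not show that it occurs.

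If the more depressed control mothers are lost more often, the observed control mean is too low and the benefit is understated. The reverse pattern overstates it. Either way, the headline estimate would carry a bias that data already collected could reduce.

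**Working it through.** **1. The plan's own figures.** Inputs from the sample-size section: difference 2.0, SD 4.5, allocation 1.5:1, alpha 0.05 (taken as two-sided), power 80%, cluster size 7, ICC 0.03, attrition 15%.

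- Control n = (1 + 1/1.5) × (1.96 + 0.84)² × 4.5² / 2.0², which gives 67, with 101 in the intervention arm: 168 in all. A t-based calculation with the rounded effect size 0.44 gives 68.3 + 102.5 = 170.9. The stated 68 + 102 = 170 is reproduced.
- Design effect 1 + 6 × 0.03 = 1.18; 170 × 1.18 = 200.6; 200 × 1.15 = 230.
- Women without a 6-month score: 0.15 × 230 = 34.5, about 35. Women with one: 195.5.
- Effective size 195.5 / 1.18 = 165.7, or 66.3 control and 99.4 intervention. SE = 4.5 × √(1/66.3 + 1/99.4) = 0.71. Power at 2.0 is about 80%.

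**2. How bias arises.** In one arm, let p be the proportion missing and D the mean 6-month EPDS of the missing minus that of the observed. The full mean exceeds the observed mean by p × D. Ignoring covariates, the benefit is therefore understated by p(control) × D(control) − p(intervention) × D(intervention).

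- Equal p and equal D: zero.
- 20% versus 10% missing, D = 2 in both arms: 0.20 × 2 − 0.10 × 2 = 0.2 points.
- 15% in each arm: the bias is 0.15 × the difference in D, so 0.5 points needs D to differ by 0.5 / 0.15 = 3.3 EPDS points.

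**3. Simulations, first set.** The article gives no loss by arm, no 3-month retention and no 3-to-6-month correlation, so these are assumptions. SD is 4.5 and the true difference is 2.0 at both visits. Baseline correlation is 0.25, and one third of women lost at 6 months also lack a 3-month score. Loss is 10% intervention and 20% control unless stated. Ranges cover 3-to-6-month correlations of 0.5 and 0.65.

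- Strong control-only dependence (log-odds 0.25 per 3-month EPDS point; 0.25 × 4.5 = 1.1 per SD, odds ratio about 3): 6-month-only estimate 1.50 to 1.61; joint 3- and 6-month analysis 1.86 to 1.89.
- The same dependence with 15% lost in each arm: 1.62 to 1.69; joint 1.89 to 1.90.
- Weak control-only dependence (log-odds 0.10): 1.76 to 1.84; joint 1.93 to 1.96.
- Strong dependence in both arms, rates still 10% and 20%: 6-month-only 1.75 to 1.82.
- Correlation lowered to 0.3, control-only: 6-month-only 1.79 (log-odds 0.25) and 1.91 (log-odds 0.10).

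**4. Simulations, second set.** Large samples, clustering ignored, baseline correlation 0.3, 3-to-6-month correlation 0.3 to 0.7, dependence of 0.7 log-odds per SD. Size of bias in the 6-month-only estimate:

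- Same process and rate in both arms: about 0.
- Same dependence, 10% versus 22.5% lost: 0.07 to 0.23.
- Dependence in one arm only, 15% lost in each: 0.09 to 0.27.
- Opposite dependence in the two arms, 15% lost in each: 0.18 to 0.58.

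When every drop-out has a 3-month score, the joint model leaves at most about 0.02 in the biased scenarios. When half have one, it removes roughly half of the bias. When none has one, it removes nothing.

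**5. Scale.** A bias of 0.1 to 0.2 is 0.14 to 0.28 standard errors (divide by 0.71); 0.5 is 0.7. If the expected estimate fell to 1.6, power would fall from 80% to about 61%, since 1.6/0.71 − 1.96 is about 0.28. Apart from bias, the joint model shrinks the standard error by only about 1 to 4%.

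**The case against.** A reader might infer that the protocol drops every woman without a 6-month EPDS and that its primary result is therefore biased. The text does not go that far. No sentence says such women are excluded, and an analysis without imputation is compatible with a likelihood repeated-measures model. The 6-month sentence speaks of recovery, while the repeated-measures sentence is the one that names EPDS as a continuous outcome. Multiple imputation and sensitivity analyses under varied missing-data assumptions are promised. Outcomes are sought regardless of compliance, and a full analysis plan is to be agreed with the Trial Steering Committee.

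Differential loss is also undocumented. The calls come from care providers, whereas outcomes are collected by separate blinded assessors at home or a preferred place, and women unlikely to be available at 6 months are excluded. The largest biases need strong dependence in one arm or opposite dependence in the two. The article's own 2–3 day EPDS test–retest coefficient is 0.50 (95% CI −0.124 to 0.777), so a low 3-to-6-month correlation is plausible, which would shrink both the bias and the gain.

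Most of this stands, and it limits both the wording and the size of the point. It does not remove it. The only model tied to the primary time point has no 3-month term. The repeated-measures model is unranked and, as described, does not clearly give a 6-month contrast. Multiple imputation is kept out of the primary result. Deferral to an analysis plan does not fully answer this, because the article already fixes the primary missing-data rule in two places.

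**Conclusion.** The point holds in a limited form. If the single-time-point model is primary, as its link to 6 months and the secondary analysis that follows it suggest, women with only a 3-month EPDS contribute nothing to the primary estimate. If the repeated-measures model is meant instead, the article needs to say so and define its 6-month contrast.

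The size is conditional. With up to about 35 of 230 women lost, the bias is about 0 to 0.5 points of the 2.0-point target, in either direction. It is about 0.1 to 0.2 with weak dependence or a low 3-to-6-month correlation, and up to 0.5 with strong control-only dependence. Only the more contrived case of opposite dependence in the two arms goes slightly higher, to 0.58. It is nil when mechanism and rate match across arms. All these figures rest on assumed loss patterns and correlations. The joint analysis helps only for drop-outs who have a 3-month score. It fully corrects the bias only if, given arm, baseline and 3-month EPDS, loss is unrelated to the missing value. In every biased scenario where some drop-outs had that score, it moved the estimate toward the true value.

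**What to change.** Under Quantitative analysis, and in the analysis plan still to be agreed, name one primary analysis of 6-month EPDS: a linear mixed model of the 3- and 6-month scores of every woman with at least one postnatal EPDS. Fixed effects are arm, occasion, arm by occasion, baseline EPDS and the randomization variables. Add a clinic random intercept and an unstructured within-woman covariance. The 6-month arm contrast is the primary result.

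Keep the 6-month-only model as a sensitivity analysis. Keep the planned multiple imputation too, and state that its imputation model includes the 3-month EPDS. The proposed primary model is itself without imputation, so the rule stated twice in the article can stand.

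The cost is a change of wording and a few lines of code, with no new data. The downside is a slightly more complex primary model. The change concerns EPDS only: Table 1 schedules the HOME-IT at 6 months alone, so that primary outcome has no 3-month score to borrow from.

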## Discussion

There is a need to conduct research on the mental and reproductive health of adolescents, especially in low- and middle-income such as Nigeria where adolescents often constitute up to 20% of the population. Empirical data to guide national planning for adolescent health are limited in Nigeria, and more so for adolescent mental health. Furthermore, even though up to 11% of all births worldwide are to adolescents, and studies have demonstrated that they bear a large burden of common perinatal mental disorders, there is a paucity of studies demonstrating the effectiveness of interventions for such disorders as well as for improving parenting skills among adolescent mothers. RAPID is designed to fill this gap in knowledge.

## Trial status

Enrollment into the trial commenced on 15 May 2018 and is projected to end 15 November 2019. The last 6-month postnatal outcome assessment is expected to occur in August 2020.

Protocol version 3.1, 1 September 2019.

## Data Availability

The datasets used and/or analyzed during the current study are available from the corresponding author on reasonable request.

## Abbreviations

CFIR: Consolidated Framework for Implementation Research
CHEW: Community health extension workers
CHO: Community health workers
ENACT: Enhancing Assessment of Common Therapeutic factors
EPDS: Edinburgh Postnatal Depression Scale
EXPONATE: Expanding care for perinatal women with depression
GAD-7: Generalized Anxiety Disorder Assessment scale
HOME-IT: Home Inventory for Measurement of Home Environment, Infant–Toddler version
LGA: Local government area
LMIC: Low and middle-income country
MCC: Maternal care clinic
mhGAP-IG: World Health Organization Mental Health Gap Action Programme, intervention guide
PBQ: Postnatal Bonding Questionnaire
PHCW: Primary health care workers
PICSS: Parental Infant Care Social Support Scale
RAPID: Responding to the challenge of Adolescent Perinatal Depression
TMC: Trial Management Committee
TSC: Trial Steering Committee
WHOQoL-BREF: World Health Organization Quality of Life-BREF
